### Adverse events

Any adverse event and unexpected and unintended responses to the treatment reported by the patients are recorded weekly with the NRS questionnaire. A causal relationship between treatment and adverse events will be evaluated using a six-grade-scale with the terminal descriptors 1 = definitely related and 6 = unknown. Possible adverse events related to acupuncture are hematoma, pain, nerve irritation, infection, and tiredness. An accidental irradiation of the eyes is regarded as the only relevant adverse event related to Laserneedle® treatment [40].

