## Background

Diabetic peripheral neuropathy (DPN) is the most common complication of diabetes mellitus with significant clinical sequelae and impact on patients’ quality of life [1, 2]. DPN manifests itself on the toes and progresses in a stocking distribution [3]. Nerve damage is related to hyperglycemia. However, various other mechanisms play a role in the pathogenesis of DPN [3]. These include elevated polyol pathway activity, advanced glycation end products (AGEs), oxidative stress, growth factors, impaired insulin/C-peptide action, and elevated protein kinase C activity. These may directly affect neuronal tissues as well as vascular structures, thus compromising nerve vascular supply [4, 5].

Clinical manifestations include paresthesia, burning sensations, and neuropathic pain as well as negative symptoms like hypesthesia, hypalgesia, and pallhypesthesia. These may contribute to balance problems and unsteady gait, leading to falls [6] and an increased risk of bone fractures and hospitalization [7]. Motor symptoms, for example muscle spasm and weakness occur less frequently [3]. DPN is associated with an increased risk of ulceration and amputation of the lower extremities as well as increased healthcare costs [8–10]. Nerve damage can occur on the myelin sheath as well as at the axonal level [11]. Differentiation is achieved by nerve conduction studies (NCS) [12]. Whilst neuropathic pain and paresthesia can be palliated by anti-convulsants, tricyclic antidepressant drugs or serotonin-noradrenalin re-uptake inhibitors [13], pharmacologic management of decreased sensation is generally ineffective, thus forming a gap in treatment strategies.

During the last decades, acupuncture has become an empirical complementary treatment option for DPN. It is recommended by the World Health Organisation [14] and the National Institute of Health [15] but treatment effectiveness is still under debate. Reviews concerning acupuncture for peripheral neuropathy (PN) have found that, despite the majority of studies reporting positive results, a reliable statement of effectiveness is not possible due to methodological limitations [16–22]. Randomized controlled, blinded clinical trials of adequate statistical power and design are still pending.

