## ACUDIN acupuncture protocol

A total of 20 acupuncture points have been selected for the ACUDIN trial. All treatment sessions of needle and laser acupuncture are performed using the following point combination:

The 4 Bafeng points on both feet (Ex-LE-10) [47]. Needles are inserted to a depth of 3 to 5 mm and left in place without stimulation for 20 min. Laser needles are fixed with perforated plaster.

The 5 Qiduan points on both feet (Ex-LE-12) [47]. Needles are inserted to a depth of 1,5 to 2 mm and left in place without stimulation for 20 min. Laser needles are fixed with perforated plaster (Fig. 2).

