### Clinical examination

Clinical examinations include sensory qualities such as the perception of pain and temperature, pallesthesia and two-point discrimination, patellar and Achilles reflexes, and gait qualities. The neuropathy deficit score (NDS) [52] and the neuropathy symptom score (NSS) [52] are part of the clinical assessment. Both are validated instruments for diagnosis and progress of DPN according to the Guideline for Diabetic Neuropathy [49].

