### Questionnaires to collect participants’ opinions

Common DPN-related symptoms will be recorded weekly by questionnaires using 11-point numeric rating scales (NRS) with the terminal descriptors “no complaint” and “worst complaint possible”. Whilst NRS are well validated for painful conditions [53], our questionnaires assess not only neuropathic pain but also tingling, burning pain, feeling of heat, feeling of cold, cramps, numbness, gait impairment, impairment of daily activities, sleep disturbances, and complaint frequency.

Table 1 summarizes the plan of data collection.

**Table 1 Tab1:** Baseline and outcome parameters

	Baseline parameter	Blood parameter	Neurological assessment	NCS^f^ Parameter	Subjective Score
Week 0	Age Gender Weight Size Comorbidity Medication Duration of disease (Diabetes and DPN)	HbA_1c_^a^	Clinical examination NSS NDS^c^	Bilateral amplitudes and NCV^b^of nn. surales and tibiales	NRS^d^
Week 6			Clinical examination NSS^e^ NDS	Bilateral amplitudes and NCV of nn. surales and tibiales	NRS
Week 15	Change of medication	HbA_1c_	Clinical examination NSS NDS	Bilateral amplitudes and NCV of nn. surales and tibiales	NRS Adverse events
Weekly (treatment 1–10)	Change of medication				NRS Adverse events

^a^HbA1c= glycated hemoglobin; ^b^NCV = nerve conduction velocity; ^c^NDS = neuropathy deficit score; ^d^NRS = numeric rating scale; ^e^NSS = neuropathy symptom score; ^f^NCS = nerve conduction studies

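### The only adverse-event route described is patient report on a symptom questionnaire, so painless lesions at needled points on feet with reduced sensation may be under-counted

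*Protocol article*

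**What the plan says.** The section Adverse events of the Protocol article fixes source and instrument together: "Any adverse event and unexpected and unintended responses to the treatment reported by the patients are recorded weekly with the NRS questionnaire". The instrument is the weekly symptom questionnaire, built from 11-point rating scales. In Table 1 the entry "NRS Adverse events" stands in the subjective-score column, for treatments 1 to 10 and for week 15. Adverse events do not appear in the neurological-assessment column at any visit.

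The Background says of the disease that "DPN manifests itself on the toes and progresses in a stocking distribution", and names "negative symptoms like hypesthesia, hypalgesia, and pallhypesthesia" among its manifestations. It adds that "DPN is associated with an increased risk of ulceration and amputation of the lower extremities".

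The section Clinical examination states: "Clinical examinations include sensory qualities such as the perception of pain and temperature, pallesthesia and two-point discrimination, patellar and Achilles reflexes, and gait qualities". Two neuropathy scores are added. The skin is not named. Skin infection of the legs is an exclusion criterion at entry. Infection and hematoma are among the possible needle events that the section Adverse events lists.

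**The concern.** The stated method depends on the patient noticing the event. It is least sensitive for a lesion that does not hurt, at a site where feeling may be poor and where most needles are placed. Someone with a clear view of that site, the practitioner who disinfects it at each session, is given no recording task.

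At stake is the safety statement for needle acupuncture. Few reported skin events could mean that few occurred or that few were felt. The comparison between arms is affected too, because the skin is punctured in the needle arm only. Missed puncture lesions lower the count in that arm and pull the difference from laser towards zero.

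**Working it through.** The documents state no adverse-event rate and no detection share, so there is no plan figure to reproduce. The check is mainly textual, followed by an illustration on assumed values.

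**1. Where the treatment goes** (ACUDIN acupuncture protocol). Bafeng 4 × 2 = 8, Qiduan 5 × 2 = 10, Lianqiu 1 × 2 = 2, total 20. On the feet: 8 + 10 = 18 of 20, or 90%. With 10 sessions, each needle patient has 18 × 10 = 180 foot insertions. For 60 patients that is 10,800. This describes exposure only; no lesion rate follows from it.

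**2. Which routes into the record are described.**

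| Place in the Protocol article | What it gives |
|---|---|
| Adverse events | Patient report, on the weekly questionnaire |
| Table 1 | Adverse events beside the rating scales, treatments 1–10 and week 15 |
| Clinical examination | Sensation, reflexes, gait, two scores; skin not named |
| Verum needle and verum laser acupuncture | Practitioner disinfects the skin; no recording task |
| Placebo laser acupuncture | Same steps as verum laser; no recording task |

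Patient report is the one described route.

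**3. What incomplete reporting would do (assumptions).** Let p be the true risk per patient of a painless skin lesion or infection, and s the share reported. Both are assumed. With n = 60 per arm:

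- expected recorded cases = 60 × p × s
- chance of recording at least one = 1 − (1 − p × s)^60

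| p | s = 1 | s = 0.75 | s = 0.5 | s = 0.25 |
|---|---|---|---|---|
| 2% | 1.2; 0.70 | 0.9; 0.60 | 0.6; 0.45 | 0.3; 0.26 |
| 5% | 3.0; 0.95 | 2.25; 0.90 | 1.5; 0.78 | 0.75; 0.53 |
| 10% | 6.0; 0.998 | 4.5; 0.99 | 3.0; 0.95 | 1.5; 0.78 |

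Each cell gives expected cases, then the chance of at least one. Worked cell: p = 0.05 and s = 0.5 give p × s = 0.025, 60 × 0.025 = 1.5, and 1 − 0.975^60 = 0.78. At s = 1 nothing is lost.

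If s is the same in all arms, a true excess risk d in the needle arm is recorded as d × s. For example, 5 percentage points would appear as 2.5 at s = 0.5.

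**The case against.** The strongest reply is that silence is being read as a rule. The article never says that staff observations are excluded. Grammatically, the reference to patients' reports could attach only to the unexpected responses. The list in the clinical examination is open-ended, and a condensed article may leave adverse-event procedures to a fuller protocol. This stands against any claim that events are captured only by patient report. It does not remove the point: on either reading the recording instrument is the symptom questionnaire, and Table 1 independently files adverse events under subjective scores. The planned causality grading rates events already recorded and adds none.

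A reader might infer that the trial population is defined by insensate feet. The documents do not support this. Entry requires clinically confirmed neuropathy and abnormal nerve conduction; sensory loss is a listed manifestation, not a criterion.

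A reader might also infer that lesions will be missed. That is not shown either. Hematoma and infection can be seen without being felt, and staff handle the feet at each session.

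A third inference, that heat lesions in the laser arm are equally at risk, runs against the section Laser acupuncture device, which describes very low heat development and no unintended effects in previous investigations. Laser needles also do not enter the skin.

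Finally, safety is neither a primary nor a secondary endpoint, and differences in sensory loss should balance across randomised arms. Both are fair and limit the weight of the point. Randomisation does not balance puncture itself, however, which occurs in one arm by design.

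**Conclusion.** The point holds in a limited form. The only adverse-event route described is patient report on the weekly symptom questionnaire. Because 18 of the 20 treated points are on feet that may have reduced sensation, painless puncture-site lesions or infections may be under-counted, mainly in the needle arm.

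The documents give no figure for the size of any under-count. The table of expected cases rests wholly on assumed risks of 2% to 10% and assumed reporting shares of 0.25 to 1. It shows direction and plausible scale, and must not be quoted as an estimate. No efficacy result is touched. This is an inexpensive improvement to safety data, not an error that invalidates the design.

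**What to change.** Keep the questionnaire and add one observed item to the weekly adverse-event record. At skin disinfection in every session the practitioner notes any visible skin break, redness, swelling, hematoma or sign of infection at the treated points. The item and its wording are identical in all three arms. Report observed and patient-reported events separately.

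Do not add the item to the neurological examinations at weeks 6 and 15. Those assessors also perform the nerve conduction studies that give the primary endpoint, and they are meant not to know the type of treatment. Week 6 falls within the 10-week treatment period, and looking for skin changes at the treated points could reveal needle versus laser.

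The cost is one more form line, with no extra staff or visits. Three limits should be accepted openly:

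- Recorded event rates may rise.
- The practitioner knows needle versus laser when recording, although not verum versus placebo laser.
- The first session gives a baseline, so sessions 2 to 10 yield nine later observations (10 − 1 = 9). Events after the tenth session still depend on patient report at week 15.

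If data collection is too advanced to change the form, state this limit in the report and do not read a low count of reported skin events as evidence that few occurred.

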### Timelines

Recruitment started in August 2011. Data collection started in January 2012. The ACUDIN trial is due to finish in 2017.

## Discussion

DPN is a common complication of diabetes mellitus [1, 2]. Conventional medicine offers symptomatic pharmaceutical treatment for DPN masking neuropathic pain and paresthesia [13]. Unfortunately, these treatments are not always effective [3] and patients have to cope with medication side-effects [55]. Furthermore, there is no treatment for sensory loss, unsteadiness, and gait-impairment, causing a gap in medical care for diabetic patients and giving reason for extending the range of treatment options.

Acupuncture has been in use for decades for the treatment of DPN and positive results have been reported on the basis of empirical knowledge and a number of pilot studies [16–22]. However, the effectiveness of acupuncture is still under debate because of the lack of high-quality clinical research.

The peripheral nervous system has the ability of regeneration in relation to repair mechanisms and in the phenomena of spreading and sprouting [56]. In DPN, morphologic peripheral nerve regeneration is impaired and inadequate nerve regeneration contributes to the pathophysiologic mechanism of DPN [57]. However, the findings of our pilot study mention a possible improvement of NCS parameters following acupuncture treatment in DPN, indicating a certain amount of neural repair [25, 26]. Parallel to improved NCS, patients have experienced subjective improvement after acupuncture treatment compared to no specific treatment, but experienced the best medical care where positive and negative DPN-related symptoms were concerned [25]. The acupuncture protocol of the pilot studies using distal and local points on the lower extremities is taken as the basis for the ACUDIN study design because other concepts failed to show efficacy [23].

This paper presents the protocol for the prospective, randomized, placebo-controlled, partially double-blinded, three-armed clinical ACUDIN trial for testing the hypothesis that classical needle acupuncture and laser acupuncture improve objective NCS parameters, as well as clinical and subjective symptoms in DPN compared to placebo treatment. NCS has rarely been used as an objective parameter in acupuncture research [24–26, 58–62]. The ACUDIN trial is the first study using NCS as an evaluation method of acupuncture treatment of DPN of the lower extremities in the form of a randomized, partially double-blinded design type.

DPN may have a strong negative impact on patients’ quality of life [13]. However, healthcare systems can encompass increased use of resources and costs which may escalate according to the severity of the disease [8–10]. Acupuncture treatment can offer a cost-effective treatment option in comparison with conventional medicine [63, 64].

The findings of the ACUDIN trial may establish the value of complementary acupuncture treatment for the potential improvement of peripheral nerve function and clinical symptoms; in addition, the findings may also lead to a reduction of the socio-economic burdens caused by DPN.

## Abbreviations

ACUDIN: ACUpuncture and Laser Acupuncture for treatment of DIabetic peripheral Neuropathy
ANOVA: Analysis of Variance
DPN: Diabetic Peripheral Neuropathy
HbA_1c_: Glycated Hemoglobin
HMC: HanseMerkur Center for Traditional Chinese Medicine at the University Medical Center Hamburg-Eppendorf, Germany
MNAP: Motor Nerve Action Potential
MNCV: Motor Nerve Conduction Velocity
NCS: Nerve Conduction Study
NCV: Nerve Conduction Velocity
NDS: Neuropathy DeficitScore
NRS: Numeric Rating Scale
NSS: Neuropathy Symptom Score
PN: Peripheral Neuropathy
RCT: Randomized Controlled Trial
SNAP: Sensory Nerve Action Potential
SNCV: Sensory Nerve Conduction Velocity
UKE: University Medical Center Hamburg-Eppendorf
WHO: World Health Organisation
